## Discussion

3.

The INTEGRActiv study will address the scientific and societal challenge of identifying integrated markers reflecting both PA level and health (PA-health biomarkers) in children and adolescents, who represent an important target population to address personalized interventions to improve future metabolic health at a societal level. Implementation of the use of the biomarkers relating PA level and health to be identified in the INTEGRActiv study will help the objective assessment of the actual benefits of public health education interventions and PA programs addressed to children and adolescents that are often developed through schools and the primary health care systems. It can also help identify non-responders requiring special attention so that PA programs more adapted to their characteristics can be recommended. Such public programs are urgently required because unhealthy PA habits among children and adolescents are very prevalent in many countries, going hand-in-hand with a high prevalence of overweight and obesity, and there is the awareness that good physical (and nutritional) habits need to be promoted especially in children and youths for their incorporation into their lifestyle, hence ensuring better adherence throughout life. Furthermore, appropriate levels of PA in these critical stages of development might also be required to ensure a proper biological metabolic programming of long-term health.

All in all, the INTEGRActiv study is expected to encompass relevant progress beyond the state-of-the-art for (a) the definition of potential biomarkers for PA level in childhood and adolescence; (b) the provision of relevant mechanistic information for the link between PA and metabolic health in young subjects; (c) the identification of factors such as age, gender, body weight, sleep behaviour and pubertal status that quantitatively affect biomarker responses; (d) the use and development of new tools in biomarker research, including integrative analysis; (e) further assessment and first-step validation of promising candidate biomarkers in an intervention study. It is expected that newly identified robust biomarkers reflecting PA level and its relation with health (PA-health biomarkers) will guide nutritional/lifestyle and clinical advice and public policies related to endorsing biomarker-based personalised PA, with better adherence and response, to promote health and prevent disease risk factors, starting in the early stages of life.

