### Aim and setting of the study

2.1.

The main objective of the INTEGRActiv study is to identify novel useful integrative biomarkers of PA level and its effects on body health (PA-health biomarkers) in children and adolescents and to carry out a first validation stage. The identification of novel candidate biomarkers will be achieved by combining measures of PA and cardiorespiratory and muscular fitness assessment with anthropometric measures, measures of cardiovascular risk factors, endocrine markers, cytokines, and circulating miRNA in plasma, gene expression profile in blood cells, and metabolomics profile in plasma in prepubertal and pubertal children/adolescents in different categories of BMI *z*-score. Besides the influence of BMI, age, pubertal state, and gender, possible confounding factors such as diet and lifestyle-related factors including sleep behaviour will be considered. It is expected that newly identified biomarkers reflecting PA level and its relation with health may guide clinical and nutritional/lifestyle advice and public policies related to endorsing personalized PA, with better adherence and response, to promote health and prevent disease risk factors since early stages of life.

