#### Participants

2.3.1.

A total of 180 volunteers (core cohort) will be recruited and distributed into two age groups: prepubertal individuals (*n* = 90), including children, from 8 to 10 years, and postpubertal adolescents (*n* = 90) from 13 to 15 years. Each group will include three subgroups (*n* = 30) of subjects with normal weight (NW), overweight (OW), and obesity (OB) as defined by WHO criteria (38). Volunteers will be equally distributed between both sexes in each group and subgroup. The sample size of the core cohort is based on our previous expertise in different projects aimed at identifying biomarkers (mainly gene expression biomarkers analysed in blood cells by omics techniques), in which we used even a lower number of volunteers [e.g., studies (24, 39)]. Moreover, the combination/integration of different types of biomarkers that will be performed (based not only on gene expression, but also considering lipidomic, metabolic and miRNA profiles) makes its more likely to be able to detect significant metabolic differences and more robust biomarkers. Additionally, the number of volunteers of the core cohort is also expected to be sufficient to achieve the required sample size for the intervention study, which was calculated as explained in Section 2.4.

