Recruitment of children/adolescents will be performed through public advertisement, among the patients of the Cardiovascular Risk Unit of the Pediatric Department of the General University Hospital of Valencia (Spain), among patients of primary care pediatricians, as well as in recruitment campaigns in sports academies and summer camps. Children/adolescents will be informed of the study, and those who express interest and meet the specific requirements of the different groups in the core cohort will be selected for recruitment. Priority will be given to individuals expressing interest in the subsequent intervention to guarantee the minimum number of volunteers required. Pubertal assessment will be performed by experts in pediatric endocrinology. Children/adolescents with regular medication, reported pathologies, and/or the presence of eating disorders will be excluded to avoid potential confounding factors. Individuals with clinical recommendations against the performance of PA will be also excluded. Screening of eating disorders will be done using the SCOFF and DEBQ questionnaires (40, 41). During recruitment, all volunteers will be informed that they will have the possibility to participate in a 6-month duration educational intervention (see below).

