#### Integrated analysis

2.6.1.

Data from the PA endpoints (PA, muscular fitness, and CRF describing variables) collected for each individual will be mapped in a principal component analysis plot. Hierarchical cluster analysis will be applied to the PCA scores in order to extract 3 clusters corresponding to low, medium, and high PA scores. The significant differences between the group of individuals will be challenged in a supervised partial-least square discriminant analysis (cross-validation ANOVA and permutation test). All the collected biological data, whether clinical or omics, will be examined in each of the 3 groups of individuals defined therefrom (low, medium, and high PA outcomes). Variables selection to fit the class assignment will be performed independently for each kind of variable with a sight of sparsity. PLS-discriminant analysis (orthogonalized or not), sparse-PLS, and machine-learning methods such as random forest will be applied and resilient variables, selected with all the methods, retained. Statistical models will be built on 4/5 of the population, and their performance assessed by predicting the 1/5 unknowns. This will be iterated 10 times. Complementary AUROC analyses will confirm biomarkers selection robustness. The most resilient variables (expected ∼20 variables from any origin) will be saved, and computed in a final PLS-discriminant analysis. From there, an equation calculated from the beta score of the PLS algorithm and the variable values will be established (using the NIPALS algorithm) to give each individual a score value (with 95% confidence intervals) that fits its PA class (e.g., low, medium, high). This equation will be challenged in the subgroup of the core cohort after the educational intervention. Also, the predictive robustness of the individual score value will be challenged to identified confounding factors (BMI, age, pubertal state, and gender, diet and lifestyle-related factors including sleep behaviour) in a logistic regression model.

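### With only 8–10-year-old prepubertal and 13–15-year-old postpubertal participants, the promised effect of pubertal status on the biomarkers cannot be told apart from age

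*Protocol article*

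**What the plan says.** Section 2.3.1 (Participants) builds the cohort from two groups: "prepubertal individuals (*n* = 90), including children, from 8 to 10 years, and postpubertal adolescents (*n* = 90) from 13 to 15 years". Each is divided into three weight classes of 30. Recruitment is limited to those groups: "those who express interest and meet the specific requirements of the different groups in the core cohort will be selected for recruitment". No group covers the years between the bands or a mid-pubertal stage.

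The abstract's discussion paragraph expects the study to show how a list of factors, age and pubertal status among them, quantitatively affects the biomarkers. Item (c) of the expected advances in section 3 (Discussion) repeats this as "the identification of factors such as age, gender, body weight, sleep behaviour and pubertal status that quantitatively affect biomarker responses".

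Section 2.6.1 (Integrated analysis) will test the individual PA score against "identified confounding factors (BMI, age, pubertal state, and gender, diet and lifestyle-related factors including sleep behaviour) in a logistic regression model". Here age and pubertal state are two entries in one list of confounders.

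Section 2.1 (Aim and setting) describes the population differently, as "metabolomics profile in plasma in prepubertal and pubertal children/adolescents in different categories of BMI". The abstract and section 2.3.1 say *postpubertal*.

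Pubertal status is assessed by specialists (section 2.3.1). Pubertal stage and date of menarche are recorded at interview (section 2.3.2.2).

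**The concern.** Age and pubertal status are named as two factors whose quantitative effects will be identified. By design, every prepubertal participant is in the younger band and every postpubertal participant in the older one. To say what puberty does beyond age, one must compare the two pubertal states at the same age, and the cohort contains no such pair. A model can still produce a puberty coefficient, but only by carrying the age trend seen inside the bands across years in which nobody was sampled.

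What is at stake is attribution. A biomarker that changes with age could be reported as responding to puberty, or the reverse. The Discussion expects the biomarkers to guide lifestyle and clinical advice and public policy, so a wrong attribution, or one extended to children in mid-puberty, could be carried into that advice. The article does not acknowledge the confounding.

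**Working it through.** **The plan's own figure.** 2 age/puberty groups × 3 weight classes × 30 = 180, which agrees with section 2.3.1.

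**Inputs.** From section 2.3.1: 90 participants per group, bands 8–10 and 13–15 years. Assumed: ages uniform within each band. The article does not say whether the limits are exact or in completed years, so both readings are shown: 2-year bands (8.0–10.0 and 13.0–15.0, gap 3 years) and 3-year bands (8.0–10.99 and 13.0–15.99, gap 2 years). Also assumed: residual SD 1, a two-sided 5% test and 80% power.

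**Overlap of information.** The band means differ by 5 years under either reading, so the between-band variance of age is (5/2)² = 6.25. The within-band variance is w²/12, where w is the band width.

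| Quantity | 3-year bands | 2-year bands |
|---|---|---|
| Within-band variance | 9/12 = 0.75 | 4/12 = 0.333 |
| R² of age on group | 6.25/7.00 = 0.893 | 6.25/6.583 = 0.949 |
| Variance inflation 1/(1 − R²) | 9.3 | 19.8 |
| Standard error factor (square root) | 3.1 | 4.4 |
| 180 × (1 − R²) | 19.3 | 9.1 |

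For separating the two effects, the 180 participants carry the information of about 9 to 19.

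**Detectable effect.** Without age, the standard error of the group contrast is √(1/90 + 1/90) = 0.149, and the detectable difference is (1.960 + 0.842) × 0.149 = 0.42 SD. With linear age added, the standard error is 0.455 (3-year bands) or 0.663 (2-year bands), and the detectable difference is 1.28 or 1.86 SD.

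**Dependence on the age trend.** The figures above hold only if the age effect is linear across the gap. As a test, let the biomarker follow an S-shaped curve in age alone, with total rise 1, centred in the gap, with steepness 0.5, 1 or 2 per year and no puberty effect. Fitting group plus linear age then returns a false puberty coefficient of 0.11, 0.41 or 0.82 (3-year bands) and 0.11, 0.46 or 0.88 (2-year bands). A larger sample drawn from the same bands would not reveal or remove this error.

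**What remains estimable.** The standard error of a common within-band age slope is 1/√(180 × 0.75) = 0.086 or 1/√(180 × 0.333) = 0.129 per year. Slopes of about 0.24 to 0.36 SD per year are therefore detectable.

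**Equivalent coding.** Let m0 and m1 be the band means. Within-band age equals age − m0 − (m1 − m0) × group, so {group, age} and {group, within-band age} give the same fitted values. In the second coding the group coefficient equals the puberty coefficient plus 5 times the age slope. That is the combined contrast, and its standard error returns to 0.149.

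**The case against.** The case on the other side has four parts, and most of it stands as a limit on the point.

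- *This is not the main objective.* Section 2.1 sets out to find PA-health biomarkers and carry out a first validation, and says only that the influence of age and pubertal state will be considered. That is right. The affected item is one of five expected advances, echoed in the abstract. It is still a stated deliverable.
- *Section 2.6.1 uses age and pubertal state only for adjustment.* Also right. A reader might infer that the inflation damages the logistic model there. The document does not support that: the quantity of interest is the PA score, and collinearity between two adjustment terms does not by itself bias or inflate its coefficient. The inflation figures are for a linear model and apply only to separating age from puberty. The article also does not fix whether all listed factors enter together.
- *Age and pubertal status are not literally one variable.* A reader might conclude that the model cannot be fitted. It can: the variance inflation is finite and within-band age slopes are estimable. Recorded stage and date of menarche may add some variation, such as time since menarche among girls in the older band. None of this supplies prepubertal and postpubertal participants of the same age.
- *The article never says that the effects are separate or independent.* The list could be read as covering one developmental contrast, which the design supports. But age and pubertal status are named as distinct factors with quantitative effects, and nothing tells the reader that they cannot be separated.

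Two well-separated developmental stages are a legitimate design, and the article makes no specific claim about ages 11–12. The difference between *pubertal* and *postpubertal* is probably loose wording.

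**Conclusion.** The point holds for one secondary deliverable. With no age overlap between the pubertal groups, a prepubertal-versus-postpubertal effect separate from age cannot be shown. If it is estimated anyway in a linear model, its variance inflation is about 9 to 20, its standard error 3.1 to 4.4 times larger, and its value set by an untestable age trend over the unsampled 2 to 3 years. The sizes rest on uniform ages within bands and on the two readings of the band limits. The failure of overlap rests only on the stated groups.

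The main objective, the other listed factors (sex, body weight, sleep), the adjustment of the PA score, within-band age slopes and the combined group contrast are all unaffected. An analysis plan could not remove the problem, because recruitment bands and claims are both set in the article.

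**What to change.** - When effects of these factors on biomarkers are reported, use the two-level group (8–10 prepubertal, 13–15 postpubertal) plus age centred within band. The fitted model does not change, but the group coefficient becomes interpretable.
- Describe the group contrast as a combined age-and-puberty effect, and report age effects only within bands.
- Reword the abstract's discussion paragraph and item (c) of section 3 to match, and limit conclusions to the two bands sampled.
- Reconcile *pubertal* in section 2.1 with *postpubertal* in the abstract and section 2.3.1.

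This needs no extra participants, visits or assays. The cost is a narrower claim: the study would no longer offer a puberty effect distinct from age, or findings for the years between the bands.

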
## Ethics statement

The studies involving humans were approved by Ethics Committees of the Consorcio Hospital General Universitario de Valencia (registry number 2/2022). The studies will be conducted in accordance with the local legislation and institutional requirements. Written informed consent for participation in this study will be provided by the participants’ legal guardians/next of kin.
